#### Data collection and management

2.12.5

After confirming that participants meet the inclusion and exclusion criteria, the research screeners will collect their demographic and baseline characteristics at the appropriate time. The primary and secondary outcomes will be measured by the outcome assessors at baseline and at 12 weeks (the end of the intervention). The primary outcome will be measured again at 25 weeks (during the follow-up period.)

The research assistant will complete the quality control of data collection and data entry. The research manager will complete the collection, classification, identification, coding, and analysis of raw data.

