### Randomization and allocation concealment

2.7

Following the baseline assessment, the subjects will be randomly assigned to1 of the 4 groups (CG, CST, TCC, and CTG) at a ratio of 1:1:1:1.

The randomization list will be generated through the Statistical Analysis Software (SAS, version 9.1) by a specified research assistant who is not otherwise involved in this study. We will use consecutive numbered, sealing and opaque envelopes to achieve the allocation concealment of the participants. The research manager will inform the eligible participants of the specific allocation results after the baseline assessment is completed.

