### Blinding

2.8

Due to the specificity of the intervention project, it is impossible to implement the blind method for participants and training instructors in this experiment. However, we will specify a designated research assistant to supervise the management of random allocation sequence and to blind coding the allocation by labelling the 4 groups (CG, CST, TCC, and CTG) A, B, C, and D. Furthermore, we will clarify the specific obligations of each investigator: the research assistant and training instructors will not be allowed to participate in the evaluation of outcomes; the outcome assessors and the statistical analysts will not be allowed to participate in screening and allocating. The participants will be told not to mention training forms in front of the assessors. We will uncover the allocation sequence and blind codes after the completion of the statistical analysis.

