### Quality control

2.14

To ensure that this trial can be completed with high quality, the researcher must strictly adhere to the requirements of the trial protocol, and the participants must be strictly in accordance with the inclusion and exclusion criteria. In addition, to ensure the authenticity and credibility of the data, we will advise participants that they are free to withdraw from the study at any stage for any reason without any consequences. Of course, if possible, we will try our best to persuade the participants to undergo the last evaluation before their withdraw. Thus, we can do an intention-to-treat (ITT) analysis. The participants must be grouped according to the random allocation sequence produced by the statistical software SAS 9.1. We stipulate that assessors and statistical analysts will not participate in the recruitment and allocation of participants.

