### Limitations

3.1

As with most clinical studies, there are also obvious limitations in this study. Ideally, all participants in clinical randomized controlled trials should follow the blind method, but this is difficult to achieve in non-pharmacological trials.^[42]^ Although it is impossible to conduct blinding of both the coaches and participants in this trial, we will reduce the possible bias by blinding the assessors and data analysts.

In summary, the results of this trial are expected to clarify the synergistic effect of CST and TCC training on musculoskeletal and cardiopulmonary function in older adults and to confirm whether combined or exclusive CST and TCC training, is more effective at improving functional outcomes in the elderly.

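### As written, the research manager both tells participants their allocation and identifies, codes and analyses the raw data, which contradicts the stated separation and blinding of the data analysts

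*Protocol article*

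**What the plan says.** All references are to the protocol article.

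- **2.7 Randomization and allocation concealment:** "The research manager will inform the eligible participants of the specific allocation results after the baseline assessment is completed".
- **2.8 Blinding:** a designated research assistant oversees the sequence and the masking of the groups, described as "blind coding the allocation by labelling the 4 groups (CG, CST, TCC, and CTG) A, B, C, and D". On separation of duties, "the outcome assessors and the statistical analysts will not be allowed to participate in screening and allocating". On timing, "We will uncover the allocation sequence and blind codes after the completion of the statistical analysis".
- **2.12.5 Data collection and management:** "The research manager will complete the collection, classification, identification, coding, and analysis of raw data". The sentence before it reads "The research assistant will complete the quality control of data collection and data entry".
- **2.14 Quality control:** "We stipulate that assessors and statistical analysts will not participate in the recruitment and allocation of participants".
- **3.1 Limitations:** because participants and coaches cannot be blinded, "we will reduce the possible bias by blinding the assessors and data analysts".

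**The concern.** Participants and training instructors know the group, so the plan relies on blinding the people who measure and the people who analyse. Analyst blinding works only if whoever prepares and analyses the data cannot link a record to an arm. Sections 2.7 and 2.12.5 together give one role both the knowledge of allocation and the handling of the data.

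What is at stake is the set of judgements made on individual records before or during the analysis. These include how a record is classified and coded, how a query is resolved, and who belongs in the per-protocol set that section 2.13 calls for. Section 2.6 describes failure to train as required in words, without a number, so applying it takes judgement. A trial report that described its data analysts as blinded would also be open to challenge from its own published protocol.

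**Working it through.** No formula applies, and the plan gives no figure to reproduce. The check sets the role statements side by side.

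| Question | Answer in the article | Section |
|---|---|---|
| Who learns individual allocations by disclosing them? | Research manager | 2.7 |
| Who identifies, codes and analyses raw data? | Research manager | 2.12.5 |
| Who may not take part in screening, recruitment or allocation? | Statistical analysts (and assessors) | 2.8, 2.14 |
| When are sequence and codes opened? | After the statistical analysis | 2.8 |
| Who is said to be blinded? | Assessors and data analysts | 3.1 |

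**Step 1. Knowledge of allocation.** A person who tells each participant the result of the draw knows that participant's real group, not a letter code.

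**Step 2. Access to data.** The same role identifies and codes the raw data. It can therefore connect participants with their records, unless some barrier exists that the article does not describe.

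**Step 3. What the labels can hide.** There are 4 labels for 4 arms. Suppose a person sees records with their A to D labels and knows the true arm of one participant under each of 3 labels. The fourth then follows by elimination (4 − 1 = 3). The research manager would know the arm of every participant informed, out of a planned 384. The letters therefore cannot mask the groups from this role.

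**Step 4. Two readings of analysis in 2.12.5.**

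- *It includes the outcome analysis.* The analyst then knows the allocation. This contradicts the blinding claimed in 3.1 and defeats the purpose of keeping the codes closed under 2.8. It also breaches 2.8 and 2.14 if informing participants of their group counts as part of allocating.
- *It means data processing only.* Separate analysts may then be blind when they run the tests. The dataset they receive has still been identified and coded by someone who knows the allocation, and the blinding arrangements do not cover that stage.

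Under either reading section 2.12.5 needs correction. The first is a direct contradiction; the second leaves a narrower gap.

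**Step 5. Research assistants.** Section 2.7 has the list generated by an assistant with no other part in the trial. Section 2.8 has a designated assistant oversee sequence and codes. Section 2.12.5 gives quality control and data entry to an assistant without further description. The article does not say whether any of these are the same person.

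**The case against.** The strongest reply is that the sentence in 2.12.5 closes a list of data-handling tasks. Statistical testing has its own section, 2.13, which names nobody, and 2.8 and 2.14 speak of statistical analysts as a distinct role. The same list gives the manager collection of data, although the outcome assessors take the measurements, so it may describe oversight. On that view the manager processes data and others run blinded tests. This is a fair reading, and it is why the point is limited to what the text says. It does not remove the problem: the article places no limit on the manager's analysis, and identification and coding stay with a role that knows the allocation.

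It may also be said that a condensed article leaves delegation of roles to the full protocol. That would answer an omission. Here the article does assign the roles, and its assignments conflict with its own rules.

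Some stronger inferences are tempting, and the document does not support them:

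- *That the analysis will in fact be unblinded.* The text shows a conflict between statements, not what will happen in practice.
- *That the assistant who holds the codes also enters the data.* Their identity is not stated, so this is a question to answer, not a conflict shown.
- *That assessor and analyst blinding are the only safeguards.* The plan also has sealed opaque envelopes, trainers barred from outcome evaluation, participants told not to mention their training to assessors, and an intention-to-treat analysis.
- *That an unblinded analyst could freely pick the test.* Section 2.13 ties the choice between ANOVA and Kruskal–Wallis to a named normality test.

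**Conclusion.** The point holds as an internal contradiction. One role knows individual allocations and also identifies, codes and analyses the raw data, while the plan states that analysts are separate from allocation and blinded until the analysis is complete. On the reading most favourable to the plan, what remains is an unblinded coding stage ahead of a blinded analysis.

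The size of any resulting bias cannot be quantified from the document. Assessor blinding is untouched, so the measurement of outcomes is not called into question here. The conclusion assumes that the research manager of 2.7 and of 2.12.5 is one role, as the shared title indicates, and that no unstated barrier separates that role's knowledge of allocation from the records it codes. The text should be corrected; the intended design, with analysts kept apart from allocation, is sound.

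**What to change.** 1. In 2.12.5, assign coding and outcome analysis to the statistical analysts already named in 2.8 and 2.14, working from a dataset that carries only the labels A to D.
2. Limit the research manager to logistics and to telling participants their allocation.
3. Have per-protocol membership decided before the codes are opened, by people without access to allocation as far as the adherence data allow. The qualification is needed because adherence records can reveal the arm, and one withdrawal criterion in 2.6 applies only to the control group.
4. State whether the research assistant who does quality control and data entry under 2.12.5 is the one who manages the sequence and blind codes under 2.8. If so, separate the two tasks.

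The cost is rewording of 2.12.5 and a matching sentence in 2.7 and 2.8. The analyst role already exists in the plan, so no extra staff are needed for the main change, and neither the sample size nor the assessments are affected.

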### Statistical analysis

2.13

We will use the intention-to-treat (ITT) analysis and per-protocol subject (PPS) analysis to analyze the primary and secondary outcomes. When there is a missing data, we will use the last observation carried forward method to deal with it. The continuous variables will be expressed as the mean ± SD. All categorical variables will be expressed in terms of their standard error. After examining whether the data accord with normality test (the Kolmogorov–Smirnov test), we will use ANOVA (assuming a normal distribution) or Kruskal–Wallis (a nonparametric test) to analyze the measurement results. We will use the Bonferroni method to appropriately adjust the overall level of significance for multiple outcomes.

For all the analyses of this study a significance level of 95% (two-sided *P* < .05) will be used. All statistical tests will be conducted using SPSS Statistical Software (IBM SPSS Statistics for Windows, Version 21.0. Armonk, NY).

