### Sample size

2.2

We used change in bone mineral density (BMD) as the main effect indicator to estimate the sample size. Sample size calculations are performed to determine the number of participants necessary to detect effect sizes. Very few randomized controlled trials have examined the effect of TCC or CST on BMD in the elderly.

Based on similar previous studies^[19,20]^ and our preliminary experiment, the means with SDs of the BMD (lumbar spine) were X1 = 0.007 (SD1 = 0.098), X2 = 0.043 (SD2 = 0.108), X3 = 0.021 (SD3 = 0.0915), and X4 = 0.051 (SD4 = 0.099) in the CG, CST, TCC, and CTG, respectively. The sample sizes per group were calculated according to the formula: 

(i)with a type I error of 5% (α = 0.05) and 80% power (β = 0.10).(ii)K: groups, K = 4.(iii)Ψ: K = 4, V1 = K-1 = 3; V2 = N-1, N desirable maximum, Ψα, β, K-1,∞ = 2.17 (Obtained from statistical tables).(iv)X0 = (X1 + X2 + X3 + X4)/K = 0.0305.

We can calculate the number of samples as n≈80, considering a 20% dropout and exit rate. Thus, a minimum of 384 total participants is necessary to reach the target of 96 participants per group.

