### Withdrawal criteria

2.6

Participants who meet1 of the following conditions will be withdrawn from the trial:(i)failure to train as required after the experiment;(ii)suffer from bone or joint pain that impacts the continuation of training;(iii)unable to continue training due to other diseases;(iv)assigned to the control group but followed a regular exercise programme.

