### Follow-up period

2.10

During the 12 weeks follow-up period, all participants will be told to resume their original lifestyle without having to insist on special exercise intervention. In addition, if the participants cannot avoid an increase in exercise load, they will be required to record the details of the extra physical activity, including the type, intensity, and time. We will re-measure the primary outcomes at the end of the follow-up period.

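### LOCF, the only missing-data method named, gives zero change to participants with baseline alone and full retention to those lost after training, with bias of unknown size and direction

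*Protocol article*

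**What the plan says.** Section 2.13 names the analysis sets, "We will use the intention-to-treat (ITT) analysis and per-protocol subject (PPS) analysis to analyze the primary and secondary outcomes", and then a single method for missing values: "When there is a missing data, we will use the last observation carried forward method to deal with it". No other method is named.

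The visits that LOCF can draw on are few. Section 2.12.5 states: "The primary and secondary outcomes will be measured by the outcome assessors at baseline and at 12 weeks (the end of the intervention", and then "The primary outcome will be measured again at 25 weeks (during the follow-up period". Section 2.1 dates the end-of-training visit at 13 weeks; I treat it as the same visit and call it week 13. Between weeks 13 and 25, section 2.10 says, "all participants will be told to resume their original lifestyle without having to insist on special exercise intervention".

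Three further passages bear on who will have missing values. Section 2.2 sizes the trial "considering a 20% dropout and exit rate", with no split by arm or time. Section 2.6 withdraws participants for reasons that include "failure to train as required after the experiment", pain or other illness that prevents training and, in the control group only, taking up regular exercise. Section 2.14 says of those who leave: "if possible, we will try our best to persuade the participants to undergo the last evaluation before their withdraw".

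**The concern.** LOCF assumes that nothing changes between the last measurement and the missing one. This trial is designed around two periods in which change is expected or in question: 12 weeks of training, then 12 weeks without it.

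Before week 13, a participant with only a baseline value is given a change of exactly zero. The sample-size section assumes mean changes from 0.007 (control) to 0.051 (combined training), so zero is not the assumed mean of any arm. A participant who attends an exit evaluation is given whatever had been reached by then, which is not a week-13 value either. After week 13, the carried value presumes that all of any gain is kept, which is what the week-25 visit is there to measure.

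Section 2.6 ties withdrawal to adherence, pain and illness, so loss may be related both to arm and to outcome. The analysis also treats filled-in values as measured ones, so the reported spread is too small. At stake are the arm contrasts at week 13 and the statement about durability at week 25.

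**Working it through.** **Inputs.** All are from section 2.2. The means (SDs) are read as changes in lumbar spine BMD, the stated basis for the sample size: control (CG) 0.007 (0.098), CST 0.043 (0.108), TCC 0.021 (0.0915), combined (CTG) 0.051 (0.099). Planned loss is 20%. The plan's grand mean reproduces: (0.007 + 0.043 + 0.021 + 0.051)/4 = 0.0305. The plan gives no figure for the effect of missing data, so what follows is illustration, with assumptions marked.

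**1. Week 13, all loss before the visit, no exit evaluation (assumption).** With a share d of baseline-only participants and arm mean μ, the LOCF mean change is (1 − d)μ. At d = 0.20 in every arm:
- CST − CG: 0.8 × 0.043 − 0.8 × 0.007 = 0.0344 − 0.0056 = 0.0288, against 0.036.
- TCC − CG: 0.0168 − 0.0056 = 0.0112, against 0.014.
- CTG − CG: 0.0408 − 0.0056 = 0.0352, against 0.044.

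Each contrast shrinks by 20% relative to the effect had everyone kept training.

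**2. The same data against a treatment-policy target.** Suppose that dropouts' true change equals the control mean (assumption). The true CST mean is then 0.8 × 0.043 + 0.2 × 0.007 = 0.0358, and CST − CG is 0.0358 − 0.007 = 0.0288, the LOCF figure exactly. In general the LOCF error against this target is (d_control − d_training) × 0.007. Under assumed unequal loss, training arm first:
- 20% and 10%: −0.0007.
- 30% and 10%: −0.0014.
- 10% and 30%: +0.0014.

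The sign follows the arm with the greater loss.

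**3. Spread of the imputed data.** With zeros filled in, the within-arm variance is (1 − d)s² + d(1 − d)μ². The mean of s² is 0.009860 and the mean of μ² is (0.000049 + 0.001849 + 0.000441 + 0.002601)/4 = 0.001235. At d = 0.20 this gives 0.8 × 0.009860 + 0.16 × 0.001235 = 0.008086, and 0.008086/0.009860 = 0.82. The analysis would see about 82% of the assumed variance.

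**4. Week 25.** Let d be the share lost before week 13 (baseline only), e the share seen at week 13 but lost by week 25, D the week-13 difference from control and f the fraction truly retained. Controls are assumed to stay at 0.007, with equal loss across arms. LOCF then shows a difference of (1 − d − e)fD + eD at week 25, against a true fD. For CTG − CG, D = 0.044.
- d = 0, e = 0.20 (assumption): apparent retention is 0.8f + 0.2. At f = 0 LOCF shows 0.0088 (20%); at f = 0.5 it shows 0.0264 against a true 0.022 (60%); at f = 1 it is correct.
- d = 0.10, e = 0.10 (assumption): at f = 0 LOCF shows 0.0044 against 0; at f = 0.5 it shows 0.0176 + 0.0044 = 0.0220, equal to the truth; at f = 1 it shows 0.0396 against 0.044. The two errors oppose each other and cancel in the difference at f = 0.5. The ratio to the LOCF week-13 difference is still too high: 0.0220/0.0396 = 56%, not 50%.
- d = 0.20, e = 0: the week-25 difference is 20% too small at any f, but its ratio to the LOCF week-13 difference is right.

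**The case against.** The case for leaving the text alone has four parts.

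**Exit evaluation.** Section 2.14 tries to obtain a last evaluation before withdrawal so that an ITT analysis is possible. A reader might infer from LOCF that every early dropout is set to zero; the article does not support that. It applies only to those with no exit evaluation. The attempt is not guaranteed, however, and the value obtained is a partly trained one.

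**Estimand.** An ITT analysis is naturally read as treatment policy, and step 2 shows that LOCF can then be unbiased at week 13. This stands, but only if dropouts change like controls and loss is about equal, neither of which the article states. The 20% shrinkage is bias against the effect under continued training, not against every target.

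**Unknown pattern of loss.** The article gives one 20% figure without timing. Step 1 places all of it before week 13, and the first case of step 4 places all of it after. They are alternatives, not effects to be added. A reader might also infer that the three training arms will lose people at different rates. The documents do not support this: scheduled training time is the same in each, and the only arm-specific withdrawal criterion in section 2.6 is for the control group. Nor can it be said that the results will be biased in a known direction.

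**Scope.** Durability is not among the stated objectives, and sections 2.10 and 2.12.5 re-measure only primary outcomes at week 25, although the abstract and section 2.1 list more. This limits the reach of the week-25 part, but a scheduled repeat of the primary outcomes will be reported and interpreted. A separate analysis plan may contain sensitivity analyses, and their absence from the article is not counted here. The primary method itself, however, is fixed in the text.

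**Conclusion.** The point holds in conditional form. The article commits to LOCF as its one named method. With this visit schedule, that means zero change for baseline-only participants, a partly trained value for those with an exit evaluation, and full retention for those lost after training.

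The week-25 part is the firmer one: among people seen at week 13 and then lost, LOCF overstates persistence whenever the effect fades. With 20% lost only in that period, a fully faded effect reads as 20% retained and a half-faded one as 60%. Earlier losses can offset this in the week-25 difference.

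The week-13 part ranges from no bias (treatment policy, dropouts like controls, equal loss) to a 20% shrinkage (effect under continued training, all of the 20% lost early without an exit evaluation). In the latter case within-arm variance is also understated, at about 82% of the assumed value. All sizes rest on the article's assumed means and on patterns of loss that it does not give. The method should be changed before analysis; the point does not invalidate the design.

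**What to change.** In section 2.13, replace LOCF as the primary method by one of two options:
- multiple imputation carried out separately by arm, with baseline in the imputation model; or
- a mixed model for repeated measures in which baseline is one of the responses.

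Either keeps all randomised participants, including those with baseline only. A mixed model restricted to participants with a post-baseline value would not serve: it drops the people at issue, and for outcomes with a single post-baseline visit it reduces to a complete-case analysis.

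Use measurements taken after a participant has stopped training wherever they exist. Keep LOCF as a sensitivity analysis.

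The cost is a change of wording and somewhat more analysis work; no new visits or participants are needed. The team should confirm that its named software covers the chosen method. The downside is reliance on missing-at-random, which in effect gives people who stopped training the outcomes of similar people who continued. One further imputation that gives training-arm dropouts control-like outcomes would show how far the conclusions depend on this.

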#### Secondary outcomes

2.12.3

The balance ability will be measured by standing on the Pro-kin system (product type: PK254P; produced by Tecnobody S.r.l company, Italy) with eyes open for 30 seconds and eyes closed for 30 seconds. The Flexibility will be measured using Sit and Reach flexibility test equipment (product type: CSTF-TQ-5000, Zhongtitongfang Co., Ltd., Beijing, China). Fall risk will be assessed via the short-form Falls Efficacy Scale International.^[24]^ Activities of daily living will be assessed using the Chinese version of the Instrumental Activities of Daily Living (IADL).^[25]^We chose the VAS as the pain score, which is1 of the most commonly used pain intensity measurement (0∼4 mm can be regarded as no pain; 5∼44 mm represents mild pain; 45∼74 mm represents moderate pain; 75∼100 mm represents severe pain).^[26]^ QOL will be evaluated using the Chinese version of EQ-5D-5L.^[27]^

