#### Safety evaluation

2.12.4

Although there are few reports on the adverse events (AEs) of TCC exercise, any unexpected AEs during the intervention period such as lumbar sprain, knee or ankle sprain, and knee pain, etc. will be recorded in detail on a case report form (CRF). If serious AEs occur, the researchers will report immediately to the project leader and the ethics committee, and they will decide whether the participants need to withdraw from the research after negotiation.

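### Section 2.13 summarises all categorical variables by a standard error, which does not describe a categorical variable

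*Protocol article*

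**What the plan says.** Section 2.13 of the protocol article gives two descriptive rules in adjacent sentences. For continuous data: "The continuous variables will be expressed as the mean ± SD". For categorical data: "All categorical variables will be expressed in terms of their standard error". The second rule covers every categorical variable, and the article nowhere gives counts, frequencies or percentages as the summary for such variables.

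Two other sections show where categorical data can arise. Under Safety evaluation (2.12.4), unexpected adverse events such as sprains and knee pain "will be recorded in detail on a case report form (CRF"). Under Data collection and management (2.12.5), "the research screeners will collect their demographic and baseline characteristics at the appropriate time". The individual baseline items are not listed.

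**The concern.** The rule for continuous variables describes a distribution by its centre and spread. The rule for categorical variables does nothing equivalent. A standard error says how precisely something has been estimated. It is not a description of the data, and printed without the estimate it belongs to it carries almost no information about how participants are distributed over categories.

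What is at stake is whether descriptive tables can be read. In a four-arm exercise trial in people over 60, a reader will want to know how many participants in each arm had a sprain or knee pain, and whether the arms were alike at baseline on any categorical characteristic. A table built to the stated rule would answer neither question.

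**Working it through.** The plan states no figure on this point, so there is nothing to reproduce. The check asks whether a standard error can stand in for the summary of a categorical variable.

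**Inputs**
- Group size n = 96, the target per group in section 2.2 (Sample size).
- Proportions p = 0.10, 0.30, 0.70 and 0.90. These are assumptions for illustration; the article gives no proportion for any categorical variable.

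**Binary variable.** The standard error of a proportion is SE = √(p(1 − p)/n), which is symmetric about p = 0.5.

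| Assumed p | About how many of 96 | SE |
|---|---|---|
| 0.10 | 10 | √(0.10 × 0.90/96) = 0.0306 |
| 0.90 | 86 | √(0.90 × 0.10/96) = 0.0306 |
| 0.30 | 29 | √(0.30 × 0.70/96) = 0.0468 |
| 0.70 | 67 | √(0.70 × 0.30/96) = 0.0468 |

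**Working back from SE to p.** Given SE and n, p solves p(1 − p) = n × SE², so p = (1 ± √(1 − 4n × SE²))/2. For the 30%/70% pair, n × SE² = 0.21 and √(1 − 0.84) = 0.4, so p is 0.3 or 0.7. For the 10%/90% pair, n × SE² = 0.09 and √(1 − 0.36) = 0.8, so p is 0.1 or 0.9. Even a reader who knows the group size is left with two opposite answers.

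**Three or more categories.** Each category has its own proportion and its own standard error. No single standard error summarises the variable.

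**Where the rule applies.** Occurrence and type of adverse event (2.12.4) are categorical by nature. Baseline characteristics (2.12.5) are affected only so far as some of them are categorical, which the article does not specify. The outcomes in 2.12.1 to 2.12.3 are BMD, step test, vital capacity, blood pressure, heart rate, balance, flexibility, the short-form falls efficacy scale, instrumental activities of daily living, VAS pain and EQ-5D-5L. All are measurements or scale scores, and none is defined as a categorical endpoint.

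**The case against.** The strongest reply is that this is a drafting slip. A standard error of a proportion is computed from the proportion, so the investigators will hold the counts and would probably print them. Adverse events are recorded in detail, so no data are lost. The 30% and 70% in the example are assumed. All of this is fair, and it is why the point is minor. It does not rescue the sentence: the article does not defer to another document here but states a rule for all categorical variables, and nothing else in it gives a correct one. An analysis plan that reported counts would have to depart from that rule.

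Three stronger readings are tempting and should not be drawn.

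- *That the plan lacks a test for categorical data.* Section 2.13 names only two tests: "we will use ANOVA (assuming a normal distribution) or Kruskal–Wallis (a nonparametric test) to analyze the measurement results". They follow a normality check and are tied to measurements; the text does not say they will be applied to nominal data. A chi-square or Fisher exact test is something a condensed article may leave to the full protocol or analysis plan, so its absence is no finding.
- *That pain will be analysed in bands.* Section 2.12.3 gives millimetre ranges for no, mild, moderate and severe pain, but in parentheses, as a guide to reading the VAS. The article refers throughout to a pain score and nowhere plans a banded analysis.
- *That outcome comparisons are compromised.* No listed primary or secondary outcome is defined as categorical.

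**Conclusion.** The sentence is wrong as written, and the consequence is minor. It makes a standard error the summary of every categorical variable, and a standard error cannot do that job: under the assumed proportions, 30% and 70% at 96 per group are indistinguishable at 4.7 percentage points, and 10% and 90% at 3.1.

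The reach is limited to adverse events and whichever baseline characteristics prove to be categorical. For these, results by arm could not be read if the rule were followed literally, with no estimate beside the standard error. The conclusion that the rule is invalid does not depend on the illustrative proportions. The primary and secondary comparisons, the sample size and the type I error are untouched.

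**What to change.** Replace the sentence in section 2.13 with: *Categorical variables will be expressed as number and percentage per group.*

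This costs one sentence. It needs no change to the design, the data collected, the sample size or the outcome analyses.
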